**Fig. 1 Fig1:**
[figure not shown]
Proposed Recruitment Flow of Patients

### Participants

We plan to enroll 80 subjects into this study. Consecutive patients seen in the orthopaedic surgery clinic with hip pain that meet all inclusion/exclusion criteria will be offered the opportunity to enroll in the study. Therefore all subjects will be recruited from within the orthopaedic surgery service at Madigan Army Medical Center, after diagnosis and surgical candidacy for FAI has been established.

### Inclusion criteria (must meet all 3)

Tricare beneficiaries between the ages of 18 and 60Must have a clinical diagnosis of FAI and/or labral pathology confirmed by a combination of all the following physical examination findings:○Patient self-report of pain in the anterior hip or groin○Pain reproduced with passive or active flexion○Positive FADIR (Flexion Adduction Internal Rotation) test○Subjective relief of pain after intra-articular injectionMust be a surgical candidate for hip arthroscopy defined by (must have all 3):○No less than 2 mm of joint space based on imaging (CT scan, radiographs and MR arthrogram)○Positive crossover sign and/or alpha angle >50 deg based on imaging (CT scan, radiographs and MR arthrogram)○Failed 6 weeks of conservative management▪Conservative management includes NSAIDs, profile, patient education and exercise handouts

### Exclusion criteria

Diagnosis of hip osteoarthritis more likely (joint space narrowing less than 2 mm.)Other concurrent systemic disease that may affect the condition (cancer, rheumatoid arthritis or systemic arthralgia/arthritis)Pending litigation/workmen’s compensationWill be moving or relocating within the following 6 monthsClearing the lumbar spine reproduces the patient’s hip symptomsPregnancyHistory of prior surgery on the same hip that will be analyzed in the studyA formal course of physical therapy within the past 6 monthsUnable to give informed consent to participate in the studyUnable to speak or read or write in English

### Randomization

Group assignment will be performed using sequentially numbered opaque sealed envelopes. Once the baseline examination is complete, an investigator blind to the randomization process will open the randomization envelope indicating subject’s treatment ground assignment. Subjects will be randomized into one of two arms (Group I = Hip Arthroscopy, Group II = Physical Therapy). A random-number generator will be used to establish randomization lists prior to the initiation of the study. To minimize the risk of predicting the treatment assignment of the next eligible patient, randomization will be performed in permuted blocks of two or four with random variation of the blocking number. Individual randomization assignments will be concealed according to the following procedure. The group assignment will be recorded on a 3.5X5 inch index card. This card will be folded in half such that the patient’s group assignment will be on the inside of the fold. The folded index card will then be placed inside the envelope and the envelope will be sealed. This will prevent the possibility of the investigator holding the envelope up to the light and visualizing the patient’s group assignment through a sealed yet potentially transparent envelope.

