## Methods/design

The study will be a single site, non-inferiority, randomized controlled trial comparing two different treatment approaches (surgical and nonsurgical) for FAI.

Potential subjects will be identified through the standard referral process to the orthopedic surgery and/or physical therapy clinic. Patients are referred through the computerized Composite Healthcare System (CHCS) by providers within the Madigan Army Healthcare System. An orthopedic surgeon at Madigan Army Medical Center (MAMC) will confirm that the patient is a candidate for hip arthroscopy prior to being considered for participation in the study (as outlined in the Inclusion/Exclusion Criteria). Research investigators and/or research assistants will ensure that potential subjects meet all inclusion and exclusion criteria prior to consent. All subjects will provide written informed consent before participating in the study. The protocol received ethics approval by the Madigan Army Medical Center Institutional Review Board. All interventions provided in this study are considered standard of care and could be given to a patient as part of their treatment plan even if they were not a part of this study. An ethics review will be conducted by Madigan Army Medical Center and monitored by the US Army Medical Department Clinical Investigation Regulatory Office to ensure compliance with federal regulations for protection of human medical research subjects. Participants can request to discontinue the study at any point.

Following consent, the investigators and/or research personnel will gather demographic information and objective measures for all subjects. A subject number will be assigned for each subject; all information collected will include the subject number only. All subjects will also complete a Hip Outcome Score (HOS), International Hip Outcome Tool Score, Global Rating of Change, Self Motivational Inventory, Pain Body Diagram, pain report via the Numeric Pain Rating Scale, and the Pain Catastrophizing Scale. The primary outcome measure will be the HOS at 2 years.

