### Blinding

Based on the nature of this study, it is not possible to blind the patient or the clinician providing the intervention to the treatment received. However, the outcomes assessor will be blinded to treatment group at the follow-up time points.

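### Randomly mixed blocks of two and four serve the stated aim of unpredictable allocation poorly in a single-site trial with unblindable arms

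*Protocol article*

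**What the plan says.** The Protocol article describes the scheme twice, under Methods/design and again under Randomization. It states a purpose, "To minimize the risk of predicting the treatment assignment of the next eligible patient", and the means: "randomization will be performed in permuted blocks of two or four with random variation of the blocking number". The proportion of blocks of each size is not given.

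The setting is described elsewhere in the article:

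- Methods/design: "The study will be a single site, non-inferiority, randomized controlled trial". No stratification is described, so there appears to be a single allocation sequence.
- Participants: "We plan to enroll 80 subjects into this study". All are recruited from one orthopaedic surgery service, and eligible patients are approached consecutively.
- Methods/design: a surgeon at the centre "will confirm that the patient is a candidate for hip arthroscopy prior to being considered for participation in the study".
- Blinding: "it is not possible to blind the patient or the clinician providing the intervention to the treatment received".
- Randomization: "Group assignment will be performed using sequentially numbered opaque sealed envelopes". The card is folded so that it cannot be read through the envelope, and "an investigator blind to the randomization process will open the randomization envelope".

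**The concern.** Envelopes and folded cards stop anyone reading the current assignment. They do not stop anyone inferring it from earlier ones. With small blocks and arms that reveal themselves, a person who follows the sequence can often tell which arm is due. The second place in a block of two is always the opposite of the first, and the second place in a block of four is the opposite two times in three.

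If the person confirming candidacy or offering enrolment can anticipate the next arm, the timing or manner of the offer can depend on the patient's prognosis. The Discussion itself recognises that a surgeon may think surgery superior and face a dilemma when offering the choice. The primary outcome, the Hip Outcome Score at 2 years, is reported by patients who know their treatment. Blinded outcome assessors do not protect against selection before randomization, and adjustment for measured covariates removes only part of it.

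**Working it through.** The protocol gives no predictability figure, so there is none to reproduce.

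**Inputs.** From the protocol: block sizes 2 and 4, 1:1 allocation (40 per arm), N = 80, one sequence. Assumed: each block is of size 2 with probability p (0.5 as the base case, 0.20 to 0.99 as the range). The guesser knows the two possible sizes and every past allocation in order, but not the size of the current block.

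**First four allocations by hand, p = 0.5.** Call the first arm A.

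1. Allocation 1: chance of a correct guess 1/2.
2. Allocation 2, guess B: p × 1 + (1 − p) × 2/3 = (2 + p)/3 = 5/6, or 83%.
3. Allocation 3:
   - After AA (probability 1/6) the block must be of size 4, so allocations 3 and 4 are both certain.
   - After AB (probability 5/6) the next is 50:50.
   - Expected chance of a correct guess: 5/6 × 0.5 + 1/6 × 1 = 0.583.
4. Allocation 4:
   - After AB and one further patient, the first block was of size 2 with probability (1/2)/(5/6) = 3/5. The chance that the opposite arm follows is 3/5 × 5/6 + 2/5 × 1 = 0.90.
   - Expected chance of a correct guess: 5/6 × 0.90 + 1/6 × 1 = 0.917.

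Averages over these four:

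- Correct: (0.500 + 0.833 + 0.583 + 0.917)/4 = 70.8%.
- Certain: (0 + 0 + 1/6 + 1/6)/4 = 8.3%.
- Predictable at 80% or better: (0 + 1 + 1/6 + 1)/4 = 54.2%.

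**All 80 allocations.** The same updating was carried through the full list, exactly for blocks of 2/4 and by simulation for 4/6/8, with sizes equally likely wherever they vary.

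| Scheme | Best guess correct | Certain | Predictable at ≥80% |
|---|---|---|---|
| 2/4 (protocol) | 72.1% | 10.9% | 55.5% |
| 4/6/8 | 67.9% | 2.3% | 23.8% |
| Fixed 4 | 70.8% | 33.3% | 33.3% |
| Fixed 2 | 75.0% | 50.0% | 50.0% |

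In patients, 2/4 gives 0.721 × 80 = 58 correct guesses, 0.109 × 80 = 9 certain and 0.555 × 80 = 44 predictable at 80% or better. For 4/6/8 the counts are 0.679 × 80 = 54, 0.023 × 80 = 2 and 0.238 × 80 = 19.

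**Sensitivity to the unstated mix (blocks of 2/4).**

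| p | Best guess correct | Certain | Predictable at ≥80% |
|---|---|---|---|
| 0.20 | 71.2% | 14.6% | 43.5% |
| 0.30 | 71.5% | 13.5% | 48.9% |
| 0.40 | 71.8% | 12.3% | 56.2% |
| 0.50 | 72.1% | 10.9% | 55.5% |
| 0.75 | 73.3% | 6.5% | 53.3% |
| 0.99 | 74.9% | 0.3% | 50.2% |

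One reason for the jump at p = 0.40 is that (2 + p)/3 reaches 0.80 exactly there.

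**Sensitivity to the cut-off (equal mix).** At 85% or better the shares are 49% for 2/4 and 10% for 4/6/8. At 90% or better they are 16% and 5%. At 70% or better they are 55% and 60%, so the ordering reverses at that low cut-off.

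**The case against.** The strongest objection is that the model gives the guesser more than the documents do. The Blinding section says only that patients and treating clinicians know the treatment. It does not say that the surgeon confirming candidacy, or the staff offering enrolment, hold a complete ordered record. Under Methods/design, therapy usually starts within 1 to 2 weeks and surgery is usually scheduled within 3 months, so delivered treatment reveals allocations late and out of order. The envelope opener is described as blind to the randomization process, eligibility criteria are listed, and patients are approached consecutively. All of this stands. The figures are therefore an upper bound, and no actual selection is shown. The safeguards still leave a gap: the blindness wording covers only the envelope opener, and consecutive offering limits selective enrolment without preventing it.

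A reader might infer that over half of allocations can be guessed with high confidence whatever the mix. That is not supported: the share is 49% when 30% of blocks are of size two, and it depends on the cut-off. A reader might also infer that the scheme defeats its aim or is the most predictable one available. That is wrong too: fixed blocks of two are worse on both the correct and the certain measures, and mixing 2 with 4 cuts the certain share from 33% (fixed fours) to 11%. Finally, the gain in best-guess accuracy from 4/6/8 is modest, 58 against 54 of 80. The larger gain is in guesses held with 80% confidence or more, 44 against 19.

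**Conclusion.** The point holds as a weakness of design; the documents do not contradict themselves here. The protocol names unpredictability as the purpose of its block scheme and fixes sizes that serve it poorly where there is one sequence and the arms cannot be masked. If recruiting staff know the possible sizes and the order of past allocations, up to about 72% of assignments are guessed correctly and about 11% are certain, with equal mixing. About 55% are predictable at 80% or better, or about 44% to 56% across the mixes examined. The correct-guess rate is the steadier figure, at 71% to 75% throughout. Blocks of 4, 6 and 8 do better on all three measures. How far the risk is realised depends on who sees past allocations and who knows the sizes, which the article settles only loosely and only for the person opening envelopes.

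**What to change.** In the allocation text under both Methods/design and Randomization:

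- Generate the list with block sizes varying at random among 4, 6 and 8, prepared by someone with no part in recruitment.
- Withhold the block sizes from the surgeon who confirms candidacy and from the staff who offer enrolment.
- Extend the statement about blindness to the randomization process from the envelope opener to everyone who recruits.
- If enrolment has begun, apply the change only to unused envelopes, under a documented amendment, since the list was to be fixed before the study started.

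The work is a new list and new envelopes. The largest imbalance at any point rises from 2 to 4 patients. Even if the trial closed at that worst point, 42 against 38, the variance of a difference in means would be (1/42 + 1/38)/(1/40 + 1/40) = 1.0025 times that of an even split, which is negligible.

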### Blinding

Based on the nature of this study, it is not possible to blind the patient or the clinician providing the intervention to the treatment received. However, the outcomes assessor will be blinded to treatment group at the follow-up time points.

### Interventions

Both treatment options are standard-of-care interventions. Their allocation and dosage are described in Table 1.

**Table 1 Tab1:** Treatment Allocation and Dosage

Intervention	Subjects needed	Dosage	Follow up time (months)
Hip Arthroscopy	*N* = 40	One surgical session (to be followed by standard post-operative physical therapy by provider outside of this study)	6, 12, 24
Physical Therapy	*N* = 40	12 sessions with a physical therapist	6, 12, 24

### Hip arthroscopic surgery

The hip arthroscopy will consist of acetabular rim trimming, labral repair or debridement and femoroplasty, all as indicated based on the surgeon’s clinical judgment with input from pre-operative imaging, exam findings and intra-operative findings. Typical surgery time is approximately 2 h in duration; surgery time may fluctuate depending on the complexity of the surgery. Hip arthroscopy is typically a same-day surgery; however subjects may require an overnight stay at the discretion of the orthopedic surgeon. This is standard for how a patient would receive this intervention outside of the study.

### Physical therapy

At the first session, the examiner will perform a standardized clinical examination in order to develop a personalized impairment-based treatment plan (See Additional file 2). The six areas that will be tested include: anterior hip mobility (tested via the FABER position and Thomas test), hip flexion range of motion (ROM), prone and seated internal rotation ROM, lumbar mobility in the quadraped rock position, gluteus medius control in the lateral stepdown movement and proprioception and lower extremity neuromuscular control in the reverse lunge. Based on the specific impairments (reproduction of the primary hip pain complaint), patient’s supervised physical therapy program will incorporate joint mobilizations, mobilization with motion, therapeutic exercise, soft tissue mobility, stretching and motor control exercises to address these identified impairments (Additional files 3, 4, and 5) . The clinic program will be reinforced by a home exercise program to address the specific needs of the patient that will include 8–10 exercises by the conclusion of the 6 weeks.

### Outcome measures

The primary outcome will be the Hip Outcome Score. Secondary outcome measures will include the iHOT33, GROC, and NPRS. These will all be taken at baseline, 6, 12, and 24 months. The Self Motivation Inventory and Pain Catastrophizing Scale will also be taken at baseline and at 24 months. For our healthcare utilization analysis, we will collect healthcare utilization and associated costs that occurred for the duration of the study, and compare them between groups. We will be using the Military Health System Data Repository (MDR) for abstraction of data.

#### Hip outcome score (HOS)

The HOS is designed to assess higher level activities (i.e. those required in athletics) and has demonstrated validity in a study of patients at a mean of 3 years following hip arthroscopy [18]. Additionally, a 2011 study states that the HOS has the greatest amount of clinometric evidence (rigor of rating scales and indexes for the description of clinical phenomena). Only three published patient-reported outcome instruments utilized to assess FAI and labral pathology use clinometric evidence and the HOS was identified as the most proven instrument [25].

#### International hip outcome score (iHOT33)

The iHOT33 is a quality-of-life patient-reported outcome measure that uses a visual analog scale response format for young, active patients with hip pathology. This 33-item questionnaire includes four sections: symptoms and functional limitations, sports and recreational activities, job related concerns and social, emotional and lifestyle concerns. This outcome measure has shown to be reliable; shows face, content and contrast validity and is highly responsive to clinical change [26].

#### Global rating of change (GROC)

The GROC will be administered to patients at the initial data collection, 6 months, 1 and 2 years. The GROC questionnaire is a common, feasible, and useful method for assessing short-term outcomes and overall changes in quality of life [27, 28]. The GROC has a 15-point scale with a change of positive three points or higher demonstrating clinically significant improvement in a patient’s perception of quality of life [27].

#### Self motivation inventory

The Self-Motivation Inventory is an outcome measure that was developed to determine level of motivation. The Self-Motivation Inventory is a 40-item tool that has been found to measure an individual’s tendency to persevere independent of situational reinforcement. It has also been used to predict successful weight loss and may correlate with number of sessions attended in weight loss program [29]. This tool underwent refinement in 1980 with the original 60-item tool being tested in undergraduate male and females. Items correlating less than 0.30 were deleted. The final 40-item scale yielded an exceptionally high internal reliability (α = 0.91) suggesting that a unitary common concept is evident for the obtained factor structure. The tool is widely used and has been tested in weight loss and therapeutic exercise studies [29].

#### Numeric pain rating scale (NPRS)

A 0–10 numeric pain rating scale (‘0’ indicating no pain, and ‘10’ worst imaginable pain) will be used to assess hip pain intensity. Numeric pain scales are known to have excellent test-retest reliability [30].

#### Pain catastrophizing scale (PCS)

The PCS is a 13-item patient-report scale developed to measure the extent to which people catastrophize in response to pain. Each item is scored from 0 (‘not at all’) to 4 (‘all the time’). The PCS is reported as a total score, with higher scores indicating greater catastrophizing, and is composed of three sub-scales: Rumination (four items; e.g. ‘When I am in pain, I keep thinking about how badly I want the pain to stop’), Magnification (three items; e.g. ‘When I am in pain, I become afraid that the pain will get worse’), and Helplessness (six items; e.g. ‘When I am in pain, I feel I can’t go on’) The PCS has been shown to have high levels of internal consistency and construct validity [31, 32].

### Justification of sample size

Our power analysis was based on the effect size reported by Martin and colleagues [33] for the Hip Outcome Score. They reported MCID values of 9 and 6 points for the Activities of Daily Living (ADL) and sports subscales respectively [33]. In order to detect a significant change between groups that is clinically meaningful, we will need to enroll 20 subjects per group based on the effect size of the ADL subgroup in the Martin study. This derived minimum sample size will provide us statistical power of 80 % with an alpha of 0.05. This is the more conservative analysis. However, the follow-up time period in the referenced study was only out to 6 months whereas this study will be out to 2 years. Accounting for 10 % loss to follow-up per year, which often happens in active duty military populations that deploy or get reassigned to multiple posts, we will plan on recruiting 80 subjects.

### Data analysis

The primary analysis of effectiveness will be performed using a linear mixed-effects model that is flexible in accommodating data that is assumed to be missing at random. There will be 4 time points for measurement of each outcome (baseline, 6, 12, and 24 months). Subjects will be analyzed in the groups that they were originally allocated to. Sensitivity analyses will be performed to assess the impact of treatment cross over in the results. Descriptive statistics will be computed to characterize and compare the 2 treatment groups for assessment of baseline heterogeneity. Distributions of measured variables will be examined visually with frequency histograms and formally assessed with Kolmogorov-Smirnov and Shapiro-Wilk statistics to test the normality assumption. Levene’s test will be used to assess for violations of the homogeneity of variance assumption. Baseline comparability of groups will be tested with chi-square statistics for categorical variables and with unpaired t-tests if parametric assumptions are satisfied; Mann–Whitney U tests otherwise. All statistical tests will be performed at an alpha level of 0.05.

If one treatment is shown to be superior to the other, supplemental analyses will be performed by dichotomizing groups based on minimal clinically important differences (MCIDs) of 9 for HOS and +3 points for GROC scores. This will allow computation of absolute risk reduction, relative risk reduction, and number needed to treat (with associated 95 % confidence intervals) using failure to obtain clinically meaningful benefit as the event of interest.

Healthcare Utilization will be extracted from the Department of Defense Military Health System Data Repository (MDR) database which is the most commonly used system operated by TRICARE for research, containing direct and purchase care data. The amount and type of healthcare associated with an FAI-related diagnosis, along with related cost, will be abstracted for every patient in the study. This will include diagnostic imaging tests, medications, and specialty referrals. The amount of utilization for each category will be compared between groups.

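### The responder analysis is planned only if superiority is shown, so a trial labelled non-inferiority plans no comparison of responder proportions otherwise, and the reported benefit is overstated on average

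*Protocol article*

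**What the plan says.** The Data analysis section first sets out the primary linear mixed-effects model, then adds a conditional step: "If one treatment is shown to be superior to the other, supplemental analyses will be performed by dichotomizing groups". The cuts are "minimal clinically important differences (MCIDs) of 9 for HOS and +3 points for GROC scores". On the purpose of the step it says: "This will allow computation of absolute risk reduction, relative risk reduction, and number needed to treat". Each measure is to have a 95% confidence interval, and the event is failure to reach meaningful benefit. No other section plans a responder comparison for the case where superiority is not shown.

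Three other statements bear on this:

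- Methods/design calls the study a "single site, non-inferiority, randomized controlled trial", as does the abstract.
- Justification of sample size gives MCIDs of "9 and 6 points for the Activities of Daily Living (ADL) and sports subscales respectively" and bases 20 per group on the ADL subscale, with "statistical power of 80 % with an alpha of 0.05".
- Outcome measures has the HOS and the GROC collected at baseline, 6, 12 and 24 months. The data for a responder comparison therefore exist whatever the primary test shows.

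**The concern.** This is a stated decision rule, not a detail left to another document. It has two consequences.

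The first is incompleteness. Under a non-inferiority label, a result without superiority is one that the design anticipates. In that case nothing is planned that tells a patient or surgeon how many people in each arm improved by a meaningful amount. That is a natural question when the choice is between surgery and physical therapy.

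The second is selection. An estimate computed only after a correlated test has crossed a significance threshold is, on average, further from zero than the truth. Here the benefit comes out too large and the NNT too small. The planned confidence intervals pass through the same gate, so they do not remove the selection. An NNT is easily quoted without the rest of the analysis, so readers should know how it came to be reported.

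**Working it through.** **Inputs from the article.** 20 per group, 80% power and alpha 0.05 (Justification of sample size); 80 enrolled, 40 per arm (Participants, Table 1); 10% loss per year for 2 years; HOS cut of 9 points.

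**Assumptions, because the article gives no figure.** Two-sided testing, normally distributed change scores, and a 50% response in the reference arm (its mean change lies at the cut). An unadjusted t-test stands in for the mixed model.

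**Step 1: the planned effect.** The 20 per group cannot be reproduced, because neither the SD nor the standardised effect is stated. Solved backwards, two-sided:

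d = (1.960 + 0.842) × √(2/20) = 0.886, and 9 / 0.886 gives an SD of about 10.2 points.

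**Step 2: completers.** 80 × (1 − 0.20) = 64, or 32 per arm.

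**Step 3: true risk difference.** With a 50% reference response it is Φ(d) − 0.5:

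- d = 0.886: 0.312, NNT 1/0.312 = 3.2
- d = 0.5: 0.191, NNT 1/0.191 = 5.2
- d = 0.3: 0.118, NNT 1/0.118 = 8.5

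**Step 4: apply the condition.** Simulated trials with 32 per arm were tested at 0.05. The risk difference was averaged over those significant in the favourable direction.

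| True d | Analysis absent | True risk difference (NNT) | Mean when reported (NNT) | Ratio |
|---|---|---|---|---|
| 0.886 | about 6% | 0.312 (3.2) | 0.323 (3.1) | 1.04 |
| 0.5 | about 50% | 0.191 (5.2) | 0.268 (3.7) | 1.4 |
| 0.3 | about 78% | 0.118 (8.5) | 0.251 (4.0) | 2.1 |

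The NNT in the fourth column is the reciprocal of the mean risk difference. Averaged over all trials, without the condition, the risk difference matched the truth. With no true difference the gate opens in about 5% of trials and then shows about 0.23 (NNT about 4.3) for the apparent winner.

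**Step 5: range over the unstated SD.** For a true difference of 9 points the ratio is 1.04 at SD 10.2, 1.23 at SD 15 and 1.51 at SD 20. For 6 points it is 1.25, 1.66 and 2.13. These SDs are illustrative apart from 10.2, which is the implied one.

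**Step 6: is the planned effect plausible at 2 years?** The article notes that its source study followed patients for only 6 months, and its Discussion cites a knee trial with crossover of 30% from therapy and 6% from surgery. If crossover of that size simply diluted the effect (an assumption), d would be 0.886 × (1 − 0.30 − 0.06) = 0.57. The analysis would then be absent in about 39% of trials, with a ratio of about 1.27.

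**The case against.** The case on the other side has real force.

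- **The bias is trivial at the planned effect.** At d of about 0.886 the analysis appears in about 94% of trials, and the NNT moves from 3.2 to 3.1. This stands. A reader might infer that any NNT from this trial will be systematically and materially too favourable. The documents do not support that: larger inflation needs a true effect below the planned one or a larger SD, and the article states neither.
- **Deleting the condition does not change the number in a trial that shows superiority.** This also stands. The bias is a property of the reporting rule over repetitions, and the primary mean difference carries the same selection when it is read only after a significant test. The firmer half of the point is completeness.
- **The simulation may overstate the inflation.** The mixed model uses baseline and partial follow-up data and probably has more power than a t-test on completers. A GROC cut is selected less strongly by a test on the HOS: with an assumed correlation of 0.5, the ratio at d = 0.5 falls from 1.39 to 1.20. Both are fair cautions on size, not on direction.
- **An NNT without a demonstrated difference is a poor summary.** When the risk-difference interval includes zero, the NNT interval runs through infinity and splits into a benefit part and a harm part. This happened in roughly 84% to 96% of simulated non-significant trials. It stands, and it limits the fix: only the proportions and the risk difference should be unconditional.
- **The analysis is supplemental, and nothing forbids descriptive proportions.** True. A near-null trial would still report between-group estimates for the HOS, iHOT33, GROC and NPRS. It is too strong to read the condition as suppressing the clinical result; the comparison is simply not planned.

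A reader might also take the single HOS cut of 9 as an error, given the 6 points for sports. It is not shown to be one. The 9 agrees with the ADL subscale on which the sample size rests, and the sentence merely omits the subscale's name.

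**Conclusion.** The point holds as a minor one. The responder comparison and its risk measures depend on superiority being shown, so under the non-inferiority label the plan has no comparison of responder proportions for an outcome that the design anticipates. Where the comparison is reported, the benefit is overstated on average: by about 4% at the implied design effect, and by 1.4 to 2.1 times if the true standardised effect is 0.5 to 0.3. The direction was the same in every scenario with a true difference. The size rests on the assumed SD, normal scores, a 50% reference response and 32 completers per arm.

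Two stronger conclusions are not available. The result of this particular trial cannot be called exaggerated in advance, because the bias is an average tendency. The primary inference is not affected either, because the mixed model is not subject to the condition.

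**What to change.** Delete the condition in the Data analysis section. Suggested wording: *Whatever the primary result, the proportion in each arm reaching the MCID at 24 months (9 points on the HOS ADL subscale; +3 or more on the GROC) will be reported with the risk difference and its 95% confidence interval. A number needed to treat will be added only if that interval excludes zero.*

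If the cut of 9 is meant for something other than the ADL subscale, the sentence should say so. The remaining NNT is still selected, but the risk difference beside it is always reported.

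The cost is one or two sentences and a few lines of analysis on data already collected. The sample size, the visits and the primary model stay as they are.
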